## Abstract

**Background:**

Alcohol dependence is a significant and costly problem in the UK yet only 6% of people a year receive treatment. Current service provision based on the treatment of acute episodes of illness and emphasising personal choice and motivation results in a small proportion of these patients engaging with alcohol treatment. There is a need for interventions targeted at the population of alcohol dependent patients who are hard to engage in conventional treatment. Assertive Community Treatment (ACT), a model of care based on assertive outreach, has been used for treating patients with severe mental illnesses and presents a promising avenue for engaging patients with primary alcohol dependence. So far there has been little research on this.

**Methods/Design:**

In this single blind exploratory randomised controlled trial, a total of 90 alcohol dependent participants will be recruited from community addiction services. After completing a baseline assessment, they will be assigned to one of two conditions: (1) ACT plus care as usual, or (2) care as usual. Those allocated to the ACT plus care as usual will receive the same treatment that is routinely provided by services, plus a trained key worker who will provide ACT. ACT comprises intensive and assertive contact at least once a week, over 50% of contacts in the participant's home or local community, and comprehensive case management across social and health care, for a period of one year. All participants will be followed up at 6 months and 12 months to assess outcome post randomisation. The primary outcome measures will be alcohol consumption: mean drinks per drinking day and percentage of days abstinent measured by the Time Line Follow Back interview. Secondary outcome measures will include severity of alcohol dependence, alcohol related problems, motivation to change, social network involvement, quality of life, therapeutic relationship and service use. Other outcome variables are treatment engagement including completion of assessment, detoxification and aftercare.

**Discussion:**

Results of this trial will help clarify the potential beneficial effects of ACT for people with alcohol dependence and provide information to design a definitive trial.

**Trial registration number:**

ISRCTN: ISRCTN22775534

## Background

The use of alcohol is one of the leading contributors to ill-health and premature deaths, and is the third leading cause of disability in Europe [1]. In England approximately 4% of the population aged 16-65 are alcohol dependent [2], but access to services is limited with large regional variations. The cost of alcohol misuse to the UK economy is estimated to be £25 bn [3] and over £200 m is spent annually on alcohol treatment in England. People with alcohol dependence who are not engaged in treatment use disproportionate levels of health, social, and criminal justice services, often through unplanned care [4].

The Alcohol Harm Strategy for England highlighted the need to improve treatment services for people with alcohol dependence, particularly those with more complex needs [5] and Models of Care for Alcohol Misusers (MoCAM) supported the development of specialist delivered interventions for this population [6]. Current alcohol service provision focuses on discrete, time-limited episodes of intervention, typically of a few weeks to a few months duration and emphasises personal choice and motivation. However studies have shown that engagement is often problematic [7,8], and despite conventional treatment approximately one third of alcohol dependent patients continue to drink heavily and have poor long term outcomes [9]. For this group of patients, alcohol dependence is a chronic, relapsing disorder [10-12] and in typical practice, treatment often involves multiple episodes extending over many years.

A parallel has been drawn between the management of chronic relapsing alcohol dependence and the management of various chronic physical and mental health problems [13]. In these a 'chronic disease management' approach has become an accepted clinical model in some chronic conditions such as diabetes. This involves ongoing care extending over a prolonged period to alter the long term trajectory of the disease. In adult mental health care, ACT is an extensively researched and widely used model of care for treating unmotivated and difficult to engage patients with severe and enduring mental illness. It emphasises active engagement over an extended period [14,15]. Key features of effective ACT include: (i) rapid access to services, (ii) a small caseload, (iii) a high ratio of community to office-based appointments, (iv) assertive engagement (e.g. with multiple attempts) and (v) a shared care approach, with care coordinators working within a multidisciplinary team that meets frequently [16,17].

In the United States ACT has been shown to be effective in reducing the number and length of admissions to hospital and achieving stable accommodation. It improves patients' satisfaction and motivation for treatment [18,19], and is effective in retaining patients in care [20,21]. European studies, however, have been less supportive of ACT and no advantage over usual care has been found for clinical or social outcomes, although it has been demonstrated to improve client engagement and satisfaction with services [22]. One reason identified for the lack of ACT superiority observed in the UK is that usual care for severe mental illness duplicates several of the key elements of ACT [16,22]. No such overlap is apparent in the current treatment of alcohol dependence. Some of the features of ACT have already been individually applied to the treatment of alcohol dependence and found to improve aspects of outcome. For example, [23] used home visits as part of an aftercare package and found that these increased the likelihood of treatment completion, while a randomised controlled trial found that a flexible and extended approach to aftercare increased the time to first drink and reduced the severity of relapse [24,25]. Most recently a pilot of assertive engagement methods resulted in a significantly greater number of patients completing treatment and entering aftercare [7]. However, the potential benefits of elements of ACT in patients with alcohol dependence but without severe mental illness remain unclear as are the specific aspects of the model that might apply to this disorder.

In this article we describe the methods of an exploratory randomised controlled trial (RCT) that is designed to test the feasibility of implementing ACT for people with chronic relapsing alcohol dependence. It aims to identify both optimal and problematic elements of ACT specific to this population and to establish the potential effect size of ACT versus standard care and evaluate 'proof of principle'.

## Methods/Design

### Overview

The Assertive Community Treatment for Alcohol Dependence (ACTAD) study is a two centre single blind randomised controlled trial of assertive outreach plus care as usual (CAU) compared with a CAU control condition for people with alcohol dependence. The primary analysis will be intention-to-treat.

### Intervention

#### Assertive community treatment intervention

ACT was originally developed for patients with psychotic disorders and has become an established model of care for this population in the US and UK. Since this intervention has never been used for people with primary alcohol dependence, the research team will implement an ACT model taking into account the original model and recent research identifying effective elements in UK studies. A treatment manual will be developed by the research team together with experts in the provision of ACT and incorporating existing research evidence.

The ACT intervention will comprise the following:

(i) Maximum caseload of 15 ACT patients per ACT practitioner

(ii) Input from a multidisciplinary team (including psychiatrists, substance misuse specialists)

(iii) Regular contact (minimum of once a week; 50% of contacts outside of the service settings, either in the patients' home or neighbourhood; short frequent contacts rather than long complex contacts will be encouraged).

(iv) Assertive engagement - persistent and repeated attempts to contact, emphasis on maintaining contact and building relationships

(iii) Focus on both health and social care needs - including accommodation, leisure, occupation, and physical and mental health

(iv) Flexibility - practitioners should work flexibly with patients' goals even when these are peripheral to the addiction.

(v) Openness - practitioners are explicit about their goals both in care planning and in visits.

(viii) Going out of your way - stepping outside of professional roles and going the extra mile for patients.

(ix) Extended care - provided for a prolonged period of 1 year.

#### Training

The training will comprise a three day workshop and a one day clinical placement. The workshop will provide specialist addiction clinicians with information about ACT, its' history, implementation in mental health and the ACTAD trial. Following the workshops each practitioner will attend a one day placement with a mental health assertive outreach team. They will shadow a member of staff including attending community and home visits with patients and have the opportunity to ask questions regarding the day to day practice of providing ACT. A final training day will focus on ACT practice in addictions. A minimum of three members of staff at each site will receive the training.

### Control intervention

The participants in the control condition will receive CAU, as this provides an appropriate comparison with routine clinical practice and will address the issue of whether ACT plus CAU is more effective than CAU alone. CAU components will be actively recorded as part of the trial but are likely to include allocation of a keyworker when one becomes available, with subsequent contact as required. All contact is usually conducted at the service via an appointment based system. Participants will receive a full assessment of alcohol, social and physical health needs, and a risk assessment. CAU focuses primarily on alcohol use and promoting abstinence and relapse prevention. It includes access to medical detoxification, psychological interventions focused on drinking behaviour and available aftercare as required. CAU may also include input from specialists in addictions psychiatry, clinical psychology and social work where available. Patients are most often signposted to other relevant agencies when these services are not directly provided by the addiction treatment service. Aftercare will typically be provided outside the community addiction services. The majority of patients are discharged to primary care within 12 weeks of being allocated a keyworker unless there are significant risks identified. Failure to attend appointments also results in discharge from the service. To establish the variability of CAU for a full-scale trial, interviews will be undertaken with team leaders at each study site and an additional four national sites examining care pathways.

### Intervention fidelity

Each ACT practitioner will participate in a training course involving a series of workshops and placements prior to delivering the intervention to eligible patients. During the intervention, practitioners are encouraged to attend monthly supervisory meetings with the research team during which fidelity will be assessed and the ACT intervention will be reinforced. In addition, staff providing care to participants in both arms of the trial will complete a contact log detailing the care they provide for each patient following each contact. The log, developed from a previous study of assertive outreach in the UK [17], includes details about the mode of contact (i.e. face to face, telephone), setting, focus of contact, and the member of staff involved. This will provide a measure of the care provided to participants in each arm of the trial.

### Participants and baseline recruitment

Potential participants will be identified by staff in participating community addiction services. In services operating a triage or self-referral system, patients presenting with alcohol problems will be screened by staff on presentation. In services operating a referral only system, all referrals will be screened by a member of the clinical team. The team will identify patients in the first instance with a primary alcohol disorder, previous contact with participating addiction services for alcohol dependence, and no history of violence to treatment staff or risk to others as determined by registration under the UK Multi-Agency Public Protection Arrangement (MAPPA). All patients meeting these criteria will be contacted and asked if they would like more information about the research trial and asked for verbal consent to being contacted by a member of the research team.

Research workers will approach patients who have expressed an interest in the study and invite them to a meeting in order to discuss the study in detail. At this meeting the researchers will undertake a full screening of eligibility. Eligible patients will be given a full description of the study and provided with a written information sheet. If willing to participate, they will be invited to sign the consent form. A baseline interview will then be conducted by the research worker taking between 1-11/2hrs. Subsequently, the patient will be randomised using a secure, remote randomisation service independent of the research team, to either the intervention or control group.

Figure 1 shows a participant flow diagram for the trial, consistent with the Consolidated Standards of Reporting Trials (CONSORT) 2010 statement [26]

**Figure 1 F1:**
[figure not shown]
**Participant flow diagram**. The participant flow diagram illustrates randomisation of 90 patients with alcohol dependence to ACT plus CAU or CAU, consistent with the Consolidated Standards of Reporting Trials (CONSORT) 2010 statement.

### Eligibility

#### Inclusion criteria

i) Age18 years or over

ii) Is able to understand English sufficiently well to obtain informed consent and complete the assessment instruments

iii) Has attended an NHS Community addiction service in either of the participating Trusts for alcohol dependence on at least one previous occasion in the last five years

iv) Is alcohol dependent. The Composite International Diagnostic Interview [27] is used to establish dependence, a diagnosis characterised by craving, tolerance, a preoccupation with alcohol and continued drinking in spite of resulting harmful consequences [28].

#### Exclusion criteria

i) Unable to give informed consent

ii) Is street homeless

iii) Is diagnosed with a psychotic disorder

iv) Is in receipt of assertive outreach services or has community mental health team (CMHT) input once or more a month

v) Has a severe cognitive impairment as determined by Mini Mental State Examination score of ≤ 10 [29]

vi) Has a history of violence to staff or is registered under MAPPA

### Assessments

#### Baseline assessments

(i) Socio-demographic details - age, sex, ethnicity, marital status, living arrangement, children, living arrangements of children, education

(ii) Drinking in the previous 90 days - Timeline Followback form 90I [30]

(iii) History of drug use - Timeline Followback

(iv) Alcohol related problems - Alcohol Problems Questionnaire [31]

(v) Severity of alcohol dependence -Severity of Alcohol Dependence Questionnaire [32]

(vi) Health utility - EQ-5D [33]

(vii) Health Related Quality of life - SF-12 [34]

(viii) Motivation to change - Readiness to Change Treatment version [35]

(ix) Social network involvement - Important People and Activities Inventory [36]

(x) Health service utilisation - York Service Use Questionnaire

#### Follow up assessments

Six months and 12 months after randomisation, all participants will be followed up. A research worker, blind to treatment allocation, will arrange a convenient time to meet with the participant in order to complete the following measures:

(i) Changes in socio-demographic details - change in relationship status, living arrangements, and living arrangements of children

(ii) Timeline Followback form 90I

(iii) Drug use in previous 90 days - Timeline Followback

(iv) Alcohol Problems Questionnaire

(v) Severity of Alcohol Dependence Questionnaire

(vi) EQ-5D

(vii) SF-12

(viii) Readiness to Change

(ix) Important People and Activities Inventory

(x) York Service Use Questionnaire

(xi) Therapeutic relationship - STAR [37]

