### Statistical analysis

The main hypothesis, stated as a null hypothesis, is that CAU augmented with ACT is no more effective than CAU in reducing alcohol consumption 12 months after randomisation. The primary outcome measures will be alcohol consumption: mean drinks per drinking day and percentage of days abstinent at 12 months measured using the Timeline Followback interview. The primary analysis will be intention-to-treat in which participants will be analysed as part of their allocated group irrespective of the treatment received; this provides the most rigorous estimate of effectiveness. The primary outcome measure will be analysed using an analysis of covariance approach adjusting for known confounding variables such as baseline mean drinks per drinking day, age and gender. If the assumptions underlying ANCOVA are not met transformations will be undertaken and if transformations are not viable alternative non-parametric approaches will be used. In order to explore the impact of missing data on the primary outcome measure we will employ multiple imputation techniques and conduct sensitivity analyses to measure any effect of missing data on reported outcomes.

Continuous secondary measures will be analysed in a similar manner. Categorical variables will be analysed using chi-squared statistics and binary outcomes analysed using logistic regression controlling for known confounding variables. Estimates and the 80% confidence intervals will be presented. In addition intra-class correlation coefficients relating to therapists will be calculated and estimates of recruitment, engagement in treatment, retention will be assessed to inform any future study.

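### The between-arm analysis of STAR at 6 and 12 months is open to selection after randomisation, because many CAU participants will probably have no current keyworker to rate

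*Protocol article*

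**What the plan says.** The Abstract of the Protocol article (Methods/Design) names the therapeutic relationship among the secondary outcomes: "motivation to change, social network involvement, quality of life, therapeutic relationship and service use". Under Follow up assessments the measure is the last item in the list, "xi) Therapeutic relationship - STAR [37", and the schedule covers both arms: "Six months and 12 months after randomisation, all participants will be followed up". STAR is not in the Baseline assessments list.

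The Statistical analysis section states: "Continuous secondary measures will be analysed in a similar manner". The manner referred to is an analysis of covariance comparing the allocated groups, with adjustment for variables such as baseline drinks per drinking day, age and gender. Multiple imputation is described only for the primary outcome measure.

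The two arms have different contact plans. The Intervention section sets ACT contact at a minimum of weekly, for one year. The Control intervention section says that CAU is likely to include "allocation of a keyworker when one becomes available, with subsequent contact as required". It continues: "The majority of patients are discharged to primary care within 12 weeks of being allocated a keyworker unless there are significant risks identified". It adds: "Failure to attend appointments also results in discharge from the service".

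**The concern.** A therapeutic-relationship score needs a clinician to refer to. Whether a participant has a current one at 6 or 12 months is settled after randomisation, and the two care pathways make it differ by arm. In ACT a live relationship is planned at both visits. In CAU the usual pathway has ended for most patients within 12 weeks of allocation.

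That leaves two possibilities for a discharged CAU participant. If only current relationships are rated, the CAU scores come from a subgroup selected on risk, late allocation and attendance. If a past keyworker is rated, a relationship that ended months ago is set against a live one. A CAU participant who was never allocated a keyworker has nothing to rate in either case.

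The trial is meant to identify which elements of ACT help and which cause problems, and to inform a definitive trial. Building relationships is an explicit part of the ACT model. A STAR difference, in either direction, could therefore be read as evidence about mechanism when it partly reflects who was still in contact.

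**Working it through.** **Timing.** The 12 weeks run from keyworker allocation, not from randomisation.
- 6-month visit at about week 26: discharge comes first if allocation occurs by week 26 − 12 = 14.
- 12-month visit at week 52: discharge comes first if allocation occurs by week 52 − 12 = 40.

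The wait for allocation is not given. The 12-month case holds for almost any plausible wait. The 6-month case is conditional on a wait of no more than about 14 weeks.

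**The plan's own figure.** The only sample-size figure concerns alcohol consumption, not STAR: 35 per group followed up, effect size 0.5, alpha 0.2, power 80%, raised to 45 per group for 25% loss. With two-sided alpha, n per group = 2(1.2816 + 0.8416)² / 0.5² = 36.1, rounded up to 37; power at 35 per group is 0.79. The stated 35 is reproduced closely enough, and nothing below depends on it. Expected follow-up is 45 × 0.75 = 33.75, about 34 per arm.

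**Precision if only current keyworkers are rated.** The documents say only that the majority are discharged. The share of CAU participants able to rate is therefore an assumption, taken as 10-40%. In SD units, SE = √(1/34 + 1/n), where n is the number of CAU raters, and the 80% half-width = 1.2816 × SE.

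| CAU share rating | n | SE | 80% half-width |
|---|---|---|---|
| 100% | 34 | 0.243 | 0.31 |
| 40% | 13.6, about 14 | 0.318 | 0.41 |
| 20% | 6.8, about 7 | 0.415 | 0.53 |
| 10% | 3.4, about 3 | 0.602 | 0.77 |

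Power tells the same story. Borrowing the effect size of 0.5 and 35 per arm, power = Φ(0.5/SE − 1.2816), with SE now √(1/35 + 1/n). It is 0.79 with all CAU participants rating (n = 35), 0.62 at 40% (n = 14) and 0.35 at 10% (n = 3.5).

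**Selection.** Suppose there is no true difference, a share f of CAU participants can rate, and STAR has correlation r with remaining in contact (normal model). The CAU raters' mean is shifted by r × φ(z)/f, where z is the normal quantile at 1 − f. With r = 0.3, an assumption, the shift is 0.29 SD at f = 0.40 and 0.53 SD at f = 0.10. With r = 0 it is zero, and with r = −0.3 it has the same size and the opposite sign. A larger sample does not remove it.

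**The case against.** Four points on the other side have force.

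1. A reader might infer that CAU participants have nobody to rate and that the STAR comparison is therefore not randomised. The article does not support that. It does not limit STAR to a current keyworker, it schedules the scale for everyone, and a discharged participant could rate the last keyworker. If everyone were rated, the comparison would remain one of randomised groups. What stands is that those never allocated a keyworker would still be unrated, and that ended relationships would be set against live ones.
2. A reader might infer that most CAU participants are already discharged by 6 months. That depends on the unstated wait.
3. A reader might infer that the bias favours ACT. Those kept on for significant risks may rate lower, but discharge of non-attenders leaves the better attenders, who may rate higher. The sign cannot be determined.
4. A reader might see the lack of a baseline STAR as a conflict with the analysis section. It is not one, because the covariates named there are all available for a STAR model.

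It can also be said that the choice of rated clinician and the handling of participants without one belong in the full protocol or SAP. That is fair as far as detail goes. But the article itself commits to a between-arm analysis, and that commitment fits poorly with the CAU pathway it describes. Finally, if past keyworkers are rated, most of the precision loss in the table disappears; the question of comparability remains.

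**Conclusion.** The concern holds in a limited form. As described, the 12-month STAR analysis is likely either to rest on a CAU subgroup selected after randomisation or to compare ended relationships with continuing ones. The same applies at 6 months if keyworkers are allocated by about week 14.

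The half-widths of 0.41-0.77 SD, against 0.31 SD with full rating, rest on an assumed 10-40% of CAU participants able to rate and on only current keyworkers being rated. The size of any selection bias depends on an unknown correlation, and its direction is open.

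This is one secondary outcome in an exploratory trial. The primary outcomes and the sample size are untouched, so the point is minor to moderate.

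**What to change.** 1. Staff in both arms already complete a log after every contact (Intervention fidelity section). From these logs, report by allocated arm the proportion who had a keyworker since randomisation and the proportion in contact at 6 and 12 months. Make this the intention-to-treat comparison. It describes contact, which differs partly by design, and should not be read as quality of relationship.
2. Have STAR completed about the most recent keyworker since randomisation, and state that referent.
3. Take STAR out of the ANCOVA applied to continuous secondary measures. Report it descriptively by arm among those with a keyworker, with the number rating and the time since last contact, and say that it is conditional on a post-randomisation state.
4. If keyworker questions are added to the follow-up form, put them at the end of the interview, after the drinking outcomes. Current contact at 12 months would hint at ACT, and the assessors are meant to stay blind. Drawing on the logs avoids most of this risk.

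The cost is a summary of data already collected, a change of analysis wording, and the loss of a formal between-arm test for one secondary outcome.
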